### Sample measurement

GPower 3.1.9.2 will be used to perform the power calculations. The motor quotient of the PDMS-2 will be our primary outcome measurement.

The results of our pilot study showed that after 6 months of intervention, the motor quotient of the intervention group with patent ductus arteriosus on average was (94.33 ± 11.29), and that of the control group was (84.67 ± 6.11); therefore, the effect size was 1.06. Thus, as the α will be 0.05 and the β will be 0.05, each group should recruit 24 patients. Considering 10% potential attrition, 27 patients in each group with patent ductus arteriosus will be recruited.

The motor quotient of the intervention group with pulmonary stenosis on average after 6 months of intervention was (101.00 ± 9.90), and that of the control group was (89.00 ± 1.41); therefore, the effect size was 1.70. Thus, as the α will be 0.05 and the β will be 0.05, each group should recruit 11 patients. Considering 10% potential attrition, 13 patients in each group with pulmonary stenosis will be recruited.

The motor quotient of the intervention group with ventricular septal defect on average after 6 months of intervention was (95.00 ± 8.54), and that of the control group was (90.50 ± 7.78); therefore, the effect size was 0.55. Thus, as the α will be 0.05 and the β will be 0.05, each group should recruit 87 patients. Considering 10% potential attrition, 96 patients in each group with ventricular septal defect will be recruited.

The motor quotient of the intervention group with atrial septal defect on average after 6 months of intervention was (99.67 ± 5.43), and that of the control group was (90.80 ± 5.72); therefore, the effect size was 1.59. Thus, as the α will be 0.05 and the β will be 0.05, each group should recruit 12 patients. Considering 10% potential attrition, 14 patients in each group with atrial septal defect will be recruited.

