### Data collection, management, and analysis

Data will be entered using EpiData software designed for this study. All data will be collected, typed, and analyzed by a statistician, who will be blinded during the trial. The main investigators will check the data every 2 weeks to ensure the quality. All statistical analyses will be performed using SPSS 20.0. Descriptive data will be presented as mean ± standard deviation. Considering that age may be a potential factor influencing the outcome measurement, a covariance analysis will be used to compare the effects between two groups. A *t* test will be used to compare changes in parent outcome measures in the two groups. Multiple linear mixed models will be used to analyze the relationships between the risk factors and the outcome measures. An intention-to-treat analysis will be used if participants are lost to follow-up. All statistical tests will be performed at a significance level of 0.05.

The parents will also be informed of this crucial aspect, and a member of the intervention team will be available any time the parents may need further information or clarification during the study period.

An interim analysis will be performed by the statistician on the primary endpoint; the statistician will be blinded for treatment allocation and will report to the main investigators. The main investigators will discuss the results of the interim analysis with the monitoring board. However, the trial will be terminated in case of harm. The criterion for stopping the trial for harm is as follows: a statistically significant difference in the primary outcome between the intervention group and a reasonable suspected causal relationship between the intervention and adverse events.

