### Harms

If there is a reasonable suspected causal relationship with the intervention, the adverse events will be reported to the Ethics Committee to guarantee the safety of the participants. We consider that there will be no risks for either group (patients with or without intervention).

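### The only stop-for-harm criterion makes an undirected significant difference in the motor quotient a necessary condition, so related harm without a motor difference cannot meet it, while benefit plus suspected related events can

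*Protocol article*

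**What the plan says.** Under Data collection, management, and analysis, the protocol article plans one interim look: "An interim analysis will be performed by the statistician on the primary endpoint". On reporting, "the statistician will be blinded for treatment allocation and will report to the main investigators", and the main investigators then discuss the results with the monitoring board.

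The same paragraph states generally that "the trial will be terminated in case of harm". It continues with "The criterion for stopping the trial for harm is as follows" and gives a single criterion: "a statistically significant difference in the primary outcome between the intervention group and a reasonable suspected causal relationship between the intervention and adverse events".

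The outcome named there is identified under Sample measurement: "The motor quotient of the PDMS-2 will be our primary outcome measurement". The significance level is set once for everything: "All statistical tests will be performed at a significance level of 0.05".

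Three other sections bear on harm:
- Harms has suspected related adverse events reported to the Ethics Committee, and also states "We consider that there will be no risks for either group".
- Data monitoring and auditing lets a board that includes independent assessors review all data and audit the trial at any time.
- Withdrawal criteria and management covers the withdrawal of an individual child after a related adverse event.

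None of the three gives another criterion for stopping the trial.

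**The concern.** A stop-for-harm rule should be met when the intervention does harm and not met when it does not. This one depends on a test of the efficacy outcome, joined by 'and' to the safety condition, and that test has no stated direction.

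Two consequences follow from the wording:
- If the programme causes adverse events but leaves the motor quotient unchanged, the criterion is not met. This contradicts the general sentence just before it.
- If the programme works, the first condition is met by benefit. Suspected related adverse events, for which no number or severity is set, then complete a criterion labelled as harm.

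The trial enrols children aged 0 to 5 years with heart disease, and this is its only stated criterion for stopping for harm. A board that applied it literally could continue when it should consider stopping, or end a successful trial under the wrong label.

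**Working it through.** **1. The plan's own figures reproduce.** Inputs are the pilot means and SDs under Sample measurement, with d = difference / sqrt((SD1² + SD2²)/2).

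| Lesion | Difference | Mean variance | d | Stated n per group |
|---|---|---|---|---|
| Patent ductus arteriosus | 94.33 − 84.67 = 9.66 | 82.40 | 1.06 | 24 |
| Pulmonary stenosis | 101.00 − 89.00 = 12.00 | 50.00 | 1.70 | 11 |
| Ventricular septal defect | 95.00 − 90.50 = 4.50 | 66.73 | 0.55 | 87 |
| Atrial septal defect | 99.67 − 90.80 = 8.87 | 31.10 | 1.59 | 12 |

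A two-sample t test at two-sided 0.05 with 95% power returns 24, 11, 87 and 12 per group (the 24 uses the unrounded d). A one-sided test would return 20, 9, 73 and 10, so the plan's tests are two-sided. Enrolment is 2 × (27 + 13 + 96 + 14) = 300. All four effects favour the intervention. These figures are not in dispute.

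**2. The logic of the criterion.** Let A be a significant difference in the motor quotient, and B a suspected causal link between intervention and adverse events. The criterion is A and B.

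| Situation | A | B | Literal rule | A read as intervention worse |
|---|---|---|---|---|
| Motor benefit, no suspected related events | yes | no | not met | not met |
| Motor benefit, suspected related events | yes | yes | **met** | not met |
| No significant motor difference, suspected related events | no | yes | **not met** | **not met** |
| Motor quotient significantly worse, suspected related events | yes | yes | met | met |

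Benefit alone does not meet the rule. The directional reading corrects the second row and leaves the third as it is.

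**3. How often condition A would hold.** The article gives neither the timing nor the size of the interim look. As an assumption, take a quarter to a half of the evaluable sample. That sample is 24 + 11 + 87 + 12 = 134 per arm, which gives 34 to 67 per arm. The lesion groups are combined, and the 6-month pilot effects are taken at face value.

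Two effect sizes are used:
- the plan's smallest, d = 0.55;
- a pooled value, with differences and variances weighted by the stated n. The difference is (24 × 9.66 + 11 × 12.00 + 87 × 4.50 + 12 × 8.87)/134 = 6.43. The variance is (24 × 82.40 + 11 × 50.00 + 87 × 66.73 + 12 × 31.10)/134 = 64.97, so the SD is 8.06 and d = 6.43/8.06 = 0.80.

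Power comes from the noncentral t distribution with 2n − 2 degrees of freedom and noncentrality d × sqrt(n/2), at two-sided 0.05.

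| True motor effect | 34 per arm | 45 per arm | 67 per arm |
|---|---|---|---|
| d = 0.55 | 0.61 | 0.73 | 0.885 |
| d = 0.80 (pooled) | 0.90 | 0.96 | 0.996 |
| none, either direction | 0.05 | 0.05 | 0.05 |
| none, intervention worse only | 0.025 | 0.025 | 0.025 |

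With no motor effect, related harm would therefore fail the rule 95% of the time, or 97.5% of the time if only intervention worse counts.

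**The case against.** The strongest reply is that the sentence is visibly garbled. It has lost its comparator, and it is introduced as a criterion for harm, so 'difference' most naturally means that the intervention group did worse. On that reading benefit cannot trigger the rule. This is fair, and the benefit scenario is the weaker half of the point. The reading does not touch the other half: the conditions remain joined by 'and', so adverse events without a motor deficit still do not meet the criterion.

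A second reply is that other safeguards exist: the general harm sentence, the Ethics Committee report, the board's access to all data, and withdrawal of individual children. They stand as mitigation. A reader might infer that adverse events could never stop this trial, but the documents do not go that far, because the general sentence and the board's powers leave room to act. What they show is one stated criterion that conflicts with the general sentence, and no second one.

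Three stronger readings should also be set aside:
- **That an effective programme by itself satisfies the rule.** It satisfies one of two conditions, and suspected related adverse events are needed as well.
- **That the type I error is inflated.** The article plans no early efficacy claim, and interim boundaries are commonly left to the analysis plan.
- **That blinding or the reporting line makes the rule fail.** A statistician blinded to allocation is ordinary practice and is not said to decide on stopping. Nothing says that the main investigators deliver the programme or receive results identified by arm.

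**Conclusion.** The point holds as a fault in the stated text. The only stop-for-harm criterion makes a significant difference in an efficacy outcome necessary, without direction or comparator, and so contradicts the general statement that harm ends the trial. This rests on the wording alone and needs no assumption.

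The probabilities only illustrate it. They depend on an assumed interim size, on combining lesion groups, and on pilot effects measured at 6 months; an interim look at 1- or 3-month data could show a smaller effect. A reader might infer that benefit is almost certain to meet the significance condition. That holds for the pooled effect at half the sample, but at the plan's smallest effect and a quarter of the sample the chance is about 61%. The 5% and 2.5% figures apply when there is no motor difference at all.

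It should be corrected before the interim analysis, because it concerns child safety and the criterion is wrong as written.

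**What to change.** Reconcile three statements: the general harm sentence and the specific criterion under Data collection, management, and analysis, and the Harms section with its reporting to the Ethics Committee. After revision, a significant difference in the motor quotient should not be a necessary condition for stopping for harm. If the motor quotient is kept as a harm signal, the text should name the comparator (the control group) and the direction (intervention worse). The content of the safety criterion is for the sponsor and the monitoring board to set; none is proposed here.

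A secondary suggestion is to consider sending the interim report directly to the monitoring board, since the board already exists.

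The cost is one amended protocol paragraph and the board's agreement. Sample size, visits and the planned final analysis do not change. If the secondary suggestion is taken up, the main investigators would no longer be the first to receive the interim results.

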### Harms

If there is a reasonable suspected causal relationship with the intervention, the adverse events will be reported to the Ethics Committee to guarantee the safety of the participants. We consider that there will be no risks for either group (patients with or without intervention).

### Data monitoring and auditing

A monitoring board, including independent assessors (not involved in the study) from the Shanghai Jiao Tong University School of Medicine, will review all data and can conduct an audit of the trial at any time.

### Confidentiality

Only the main investigators will be allowed back-end EpiData software entry with passwords. All children with CHD will be identified by sex, birth date, and evaluation date, and will be assigned a trial number during and after the trial in accordance with personal data protection laws.

### Access to data

The main investigators will have the right to enter the final and complete trial dataset, and there is no contractual agreement to limit such access to all the investigators.

### Ancillary and post-trial care

After completing the trial, we will continue to evaluate and treat the patients in the future according to their parents’ wishes.

### Dissemination policy

The final results of the trial are planned to be published in a scientific journal and presented at medical conferences. The final reporting will follow the Consolidated Standards of Reporting Trials (CONSORT) Statement guidelines (http://www.consort-statement.org).

## Discussion

The home-based exercise program may not only contribute to an increase in the motor performance of children when the parents are included; it may also reduce unnecessary concerns [20, 25]. We will implement appropriate guidelines and supervision for the home-based exercise program; for example, we will call the parents to remind them to carry out the rehabilitation program weekly and to answer any questions or concerns. In addition, we will hand out brochures and disks to share exercise education materials. Our study may provide replicable evidence that a home-based exercise program can improve motor abilities in children with CHD and improve parental anxiety, caregiver burden, and the overall quality of life.

### Strengths and limitations

The first strength of our study is that it will be the first randomized controlled trial that focuses on home-based exercise for young children with CHD and cardiac catheterization. Second, except for the important elements of cardiac function, our study focuses more on growth development at an early stage for children with CHD. Third, we used GPower 3.1.9.2 software for the sample calculation to ensure its scientific validity. Fourth, our study will last for 6 months, with three re-evaluations, in order to update the patients’ recovery and development status in time. Fifth, our study develops a detailed and individual home-based exercise program for each patient, and provides a one-on-one guide for the parents, until they master the skills. Moreover, there is a close home-based monitoring process, which could ensure the quality of implementation of the home-based exercise program to a certain extent. Sixth, our intervention will not solely focus on the children, as their parents will also be educated in home-based exercise and other appropriate educational and care guidelines for children with CHD.

Several limitations exist in our trial: (1) the age of subjects is limited to 0 to 5 years; (2) we only recruit patients with cardiac catheterization for our trial; we will not group the children according to their specific CHD subtypes or the treatment approach to CHD; (3) we will not evaluate language and speech development or cognitive development directly, only motor development; thus, our trial cannot be used as a comprehensive evaluation of all types of home-based exercise programs for CHD children with cardiac catheterization; and (4) our study includes a short follow-up duration of 6 months.

In conclusion, our study design for delayed motor development of CHD children with cardiac catheterization developed a home-based exercise program as the main intervention approach after the procedure. It is crucial to address whether a home-based exercise program could improve the patients’ motor abilities and improve parental anxiety, burden, and quality of life. The findings will be beneficial for children with CHD and their families, research collaborators, physicians, and the general public.

### Trial status

Patient recruitment is ongoing. Recruitment of study participants commenced on 10 January 2016.

## Abbreviations

CHD: Congenital heart disease
PDMS-2: Peabody Developmental Motor Scales-2
SOS: Speed of sound
WeeFIM: Functional independence measure instrument
